## Abstract

**Background:**

Primary dysmenorrhea (PD), is one of main gynecological complaints in women of child-bearing age. Common medications for PD do not always achieve satisfactory outcome of pain relief. Hence, both health professionals and patients are seeking help from complementary and alternative medicine. The acupoint herbal plaster (AHP), which appears to be a safe and effective way to alleviate menstrual pain, as well as to improve other PD-related symptoms. Despite similar clinical studies for this condition in the past, no high-quality methodology-based clinical trial has been reported to date. The current study aims to assess the efficacy of the AHP compared with the acupoint placebo plaster (APP) and being placed on a waiting-list control group in patients with primary dysmenorrhea.

**Methods/design:**

This study is a randomized, single-center, placebo-controlled clinical trial. A total of 180 women with PD will be included and randomly allocated to the AHP, APP and waiting-list (WL) groups in a 1:1:1 ratio. Patients in the AHP group will be provided with herbal plasters (*Shaofuzhuyu* decoction) on various acupoints: *Shenque* (CV8), *Guanyuan* (CV4), *Qihai* (CV5), *Ciliao* (BL32) and *Zigong* (EX-CA1). Women in the APP group will receive placebo plasters on the same acupoints, and no intervention will be given to the WL group until completion of the study. The primary outcome will be pain intensity reduction measured by a Visual Analog Scale (VAS), with other outcome measurements including the Cox Menstrual Symptom Scale (CMSS), the 12-Item Short Form Health Survey (SF-12) and the Participant Global Impression of Change (PGIC). All assessments will be performed at baseline, each menstrual cycle during the treatment course and the follow-up course. Any adverse events will be recorded throughout the study.

**Discussion:**

This is the first study to compare the changes in menstrual pain after three different interventions: the active intervention (AHP), the placebo intervention (APP), and a period of no intervention (WL). This three-arm randomized controlled trial (RCT) aims to investigate the relative contributions of the specific (AHP vs. APP) and non-specific (APP vs. WL) effects to the overall clinical effects of the active AHP on women with PDM. The scientific and rigorous methodology design of this trial should gather good evidence to assess the curative effects and safety of the AHP on PD. Moreover, the results of this study may provide evidence-based references for the treatment of menstrual pain in future.

**Trial registration:**

Chinese Clinical Trial Registry, ID: ChiCTR-TRC-16008701. Registered on 22 July 2016.

**Electronic supplementary material:**

The online version of this article (10.1186/s13063-018-2682-8) contains supplementary material, which is available to authorized users.

## Background

Primary dysmenorrhea (PD) is prevalent among adolescent girls and women of reproductive age [1]. The incidence of PD ranges from 45% to 72% of all menstruating women; moreover, among adolescent girls it can be as high as 93% [2, 3]. Its symptoms vary but typically include dull, throbbing and cramping pain in the lower abdomen during menstruation [4, 5]. Patients may also experience vomiting, nausea, diarrhea, fatigue, fever, headache, sleeplessness and backache [6, 7]. This widespread condition not only decreases social participation and the quality of life of women, but also causes significant financial losses due to inability to work and extra medical costs [8, 9].

Approximately 67% of patients with PD choose anodyne drugs to temporarily relieve pain [10]. Nonsteroidal anti-inflammatory drugs (NSAIDs) are well advocated as the first-line medication for PD [11]. However, the pharmacological treatment has been reported to be associated with adverse effects including indigestion, headache, drowsiness; and in 20%–25 of patients, failure to relieve the pain was reported [12]. Consequently, efforts have been made to identify effective, low-risk interventions [13, 14].

Acupuncture and moxibustion therapy has been used as a non-pharmacological analgesic method in China for hundreds of years. Some clinical studies have demonstrated that acupuncture and moxibustion can be as effective as, or even superior to, pharmacological drugs in relieving menstrual pain [15–17]. In addition, a number of systematic reviews and meta-analyses have also shown that acupuncture leads to overt reduction in the pain of dysmenorrhea [18, 19]. As a typical external treatment in acupuncture, the acupoint herbal plaster (AHP) is a non-invasive, minimal-dose, transcutaneously absorbed, pharmacological treatment modality. Technically, its performance is based on the classical acupuncture and herbal medicinal theories. The treatment starts with placing processed Chinese herbal paste on a medical sticky plaster and then applying the plaster on certain acupoints. It is used for different treatment purposes in a much gentler format but can still achieve almost the same results of needling acupuncture. The AHP has been long known for its classical use of relieving respiratory conditions including pediatric recurrent pneumonia [20], stable chronic obstructive pulmonary disease [21], asthma [22] and rhinitis [23], as well as other conditions such as acute pancreatitis [24] and male infertility [25]. Nowadays, this traditional therapy has been innovated and developed to treat a much wider range of conditions including PD. Accordingly, modern clinical observational studies [26–28] have also indicated that the AHP has the potential to safely and effectively alleviate menstrual pain and improve PD-related symptoms.

According to the basic Traditional Chinese Medicine (TCM) theory, the major actions of the AHP are promoting blood circulation and moving energy (*Qi*) within the human body. The underlying mechanism of the favorable effect of the AHP possibly originates from the dual effects of acupoint stimulation and drug actions. Based on different herbal formulas, the AHP has been reported to exert different therapeutic effects, including regulating cellular immune function, reducing pulmonary surfactant proteins, and reducing the severity of inflammation [29–32]. Modern pharmaceutical studies have demonstrated that paeoniflorin, petroleum ether-soluble fraction, eleven gingerols and others are the key chemical compound constituents within the herbs in the AHP [33–36]. The herbs that will be used in the plaster come from an ancient formula named “*ShaoFu-ZhuYu Tang*” (SFZYT).. This has been recognized as a safe and effective remedy to treat PD since the Qing Dynasty [37, 38]. An earlier pharmacological study showed that SFZYT inhibits the constriction of the uterine muscles and causes a favorable anti-inflammatory action [39]. Moreover, another study that employed PD-modeled rats indicated that the estradiol, oxytocin, progesterone, endothelin, β-endorphin and PGF2α were restored to normal levels after intake of SFZYT [33]. These bioactive components within SFZYT can be absorbed transcutaneously from the herbal plaster. Hence, they can play a crucial role in regulating the whole body.

Unfortunately, there is a lack of high-quality clinical trials until now that have assessed the efficacy and safety of the AHP for PD. Therefore, we designed this clinical trial to fill this gap. To our knowledge, this study is the first RCT to date with a placebo design to test the efficacy and safety of the AHP on PD.

## Methods/design

### Study design

This proposed study is a single-centered, randomized, placebo-controlled trial which was devised following the Consolidated Standards of Reporting Trials (CONSORT) Statement recommendations [40] and the Standardized Protocol Items: Recommendations for Interventional Trials (SPIRIT) guidelines Additional file 1 [41]. Ethical approval has been obtained from the Institutional Review Board (IRB) of the Teaching Hospital of Chengdu University of Traditional Chinese Medicine (Approval No. 2016KL–003). We registered the study on the Chinese Clinical Trial Registry (Registration No. ChiCTR-IOR-16008701) in 2016.

The study will take place in the 3rd Affiliated Hospital of Chengdu University of TCM. During a run-in period of three menstrual cycles prior to randomization, the patients will be required to complete a Dysmenorrhea Diary (DD) and record related symptom scores every month to establish an individualized baseline score. A total of 180 subjects meeting the including criteria will be allocated randomly to three research groups that include one experimental group of the AHP and two control groups of the acupoint placebo plaster (APP) group and the waiting-list WL group. After randomization, subjects in the AHP and APP groups will receive treatments for another three menstrual cycles. Follow-up assessments through telephone calls or social media smartphone application will be processed for the last period of three menstrual cycles until the completion of study. Altogether it takes 9 months of three stages with three period cycles in each session. (See Fig. 1 for the study flowchart, and Fig. 2 for the assessment schedule).

**Fig. 1 Fig1:**
[figure not shown]
Flowchart of the trial

**Fig. 2 Fig2:**
[figure not shown]
Standard Protocol Items: Recommendations for Interventional Trials (SPIRIT) Figure of enrollment, interventions and assessments. *VAS* Visual Analog Scale, *CMSS* Cox Menstrual Scale, *SF-12* 12-Item Short Form Health Survey, *PGIC* Participant Global Impression of Change, *CEQ* Credibility Expectancy Questionnaire

### Participants

#### Recruitment strategies

Study participants will be recruited mainly from the outpatient and inpatient sections of the Gynecology Department. Additionally, through flyers and social media advertisements, participants will be recruited from local communities and university campuses. All patients have the right to participate or drop out at any time, and will be required to sign the informed written consent before any study procedures commences.

#### Inclusion criteria

Participants who, in line with the following criteria, will qualify for the study are: (1) nulliparous women (18–30 years old), (2) women who meet the diagnostic criteria of PD under the Primary Dysmenorrhea Consensus Guideline [11], (3) women who meet the TCM diagnosis of “*qi* and blood stagnation” or “cold and dampness retention,” (4) women who have normal menstrual cycles (occurring every 28 ± 7 days), (5) a VAS score of the menstrual pain ≥ 40 mm during the baseline menstrual period, (6) women who agree to complete a DD during the study period, (7) women who agree to sign a informed consent form and volunteer for the research.

#### Exclusion criteria

Participants from the study who meet one or more following criteria will be excluded: (1) women with secondary dysmenorrhea caused by endometriosis, polycystic ovarian syndrome, pelvic inflammation and other gynecologic diseases, (2) women with any of the serious contraindications of cardiovascular, liver and kidney diseases, (3) women who are unable to express their subjective symptoms due to intellectual or mental conditions, (4) women with a malignant tumor, (5) women with poor compliance (i.e., cannot understand the purpose of this study or complete a DD during the baseline assessment), (6) pregnancy or breastfeeding, (7) women receiving another therapy or having received any other medical inventions for PD within the last 3 months.

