In the AHP group, the standard operating procedures (SOP) are listed as follows:Prepare the herbal materials: SFZYT includes *Angelicae sinensis Radix* (*danggui*), Rhizoma (*chuanxiong*), *Paeoniae Radix rubra* (*chishao*), *Cinnamomi cortex* (*rougui*), *Foeniculi fructus* (*xiaohuixiang*), *Zingiberis rhizoma (ganjiang*), Myrrha (*moyao*), *Trogopterus dung* (*wulingzhi*), Typhae Pollen (*puhuang*) and *Corydalis rhizoma* (*yanhusuo*). The ingredients of this formula are mixed in a weight ratio of 3: 1: 2: 1: 0.5: 2: 1: 3: 1: 1 and then the raw materials ground into fine powder (under 75 μm diameter) using a special Chinese medicinal crop powder mixer (manufactured by Royalstar Co., Ltd., Hefei, China)Add the liquid base: place the mixed herbal powder into a container, add honey and stir well to make a thick herbal pasteAdd the sticky plaster: put 10 g of the herbal paste onto a medical sticky plaster. Then apply the plaster over the acupoints. The sticky plasters are sized 5 × 5 cm^2^ with a 0.8-cm radius in the middle of which is placed the host herbal paste. The rest of the sticky plaster carries no herbal paste, which makes it adhere to the skin over the acupointsTreatment procedures: locate the acupoints, disinfect the skin, and attach the plaster on the skin over the acupoints. The plasters will be left on the skin for 4–8 h depending on each patient’s individual response because it must be removed immediately should any allergic reaction occur, which may be described by patients as a burning sensation, severe itchiness, blisters, pruritus or rash on the local skin. A total of nine sessions will be performed during the three menstrual cycles, the treatment starts 1 week prior to the menstruation, with one 6–8-h treatment three times per week, according to the subject’s estimated dates

For the APP group, the placebo paste is made of buckwheat flour without any herbal medicines; however is still mixed with honey to maintain a similar appearance to the AHP (Fig. 2c and d) so that the plasters used in these two experimental groups are undistinguishable to patients and practitioners. Moreover, the only variable between the AHP group and the APP group is the ingredients of paste. In order to reduce the bias caused by performance, all the rest of the clinical procedures remain the same.

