### Safety evaluation

Clinical adverse events (AEs) will be recorded throughout the study and graded using the National Cancer Institute Common Terminology Criteria for Adverse Events (CTCAE) version 4 [55]. According to previous randomized controlled trials (RCTs) [56, 57], the AHP may cause potential adverse events of itchiness, allergic responses of the skin or the whole body, local infections and other mild side effects. Any unexpected symptoms or signs during the treatment must be documented regardless of their relation to the study intervention. All details of related and unexpected AEs, such as time of occurrence, severity of AE, and suspected causes, will be recorded on Case Report Forms (CRFs). Participants with mild and moderate AEs will receive symptomatic treatment and will be closely followed up by the research team. Severe AEs will be reported to the Research Ethics Committee within 48 h.

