#### Methods of statistical analyses

Data analyses will be processed with SPSS 22.0 (SPSS Inc., Chicago, IL, USA) and supervised by a skilled statistician blinded to group allocation.

The Full Analysis Set (FAS) is for all participants who have been randomized in terms of the intention-to-treat (ITT), and the per-protocol analysis set (PPS) and is for the individuals who complete the trial and do not have significant protocol violations. On the basis of rule of the last-observation-carried-forward, missing values will be imputed. In order to evaluate therapeutic effect and safety, the FAS and PPS will be used simultaneously.

Categorical data, such as gender and medical history, will be tabulated with frequencies or percentages; and continuous data, such as age and disease course, will be reported as mean ± standard deviation (SD), or median. For the baseline variables, sociodemographic data and other basic indicators will be carried out using analysis of variance (ANOVA) and *χ*^2^. To compare variables before and after treatment in the same group, a paired *t* test will be used. Repeated measures analysis of variance (ANOVA) will be used to compare the intergroup differences among the three groups. Tests of ITT between the AHP and APP arms and between the APP and WL arms with respect to the change will based on time-intervention interactions in the mixed-effect models. A *P* value of less than 0.05 (two-sided) indicates a statistically significant difference, with 95% confidence intervals.

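### The protocol names allergic reactions as a possible harm of the AHP, but no printed eligibility criterion excludes known hypersensitivity or damaged skin

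*Protocol article*

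**What the plan says.** The Exclusion criteria section states "Participants from the study who meet one or more following criteria will be excluded" and lists seven items: secondary dysmenorrhea; serious cardiovascular, liver or kidney disease; inability to report symptoms; malignancy; poor compliance; pregnancy or breastfeeding; and other treatment for dysmenorrhea in the preceding three months. The Inclusion criteria section also lists seven items: age and nulliparity, diagnosis, TCM pattern, cycle regularity, a VAS threshold, agreement to keep the diary, and consent.

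On harms, the Safety evaluation section says that "the AHP may cause potential adverse events of itchiness, allergic responses of the skin or the whole body", together with local infections and other mild effects. The Interventions section describes the local signs to expect, including burning, severe itch, blisters and rash, and says of the plaster that "it must be removed immediately should any allergic reaction occur". For adverse events that do occur, "Participants with mild and moderate AEs will receive symptomatic treatment and will be closely followed up by the research team".

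On exposure, the active paste is a ten-ingredient herbal powder in honey, applied under a sticky plaster. In the other plaster arm, "the placebo paste is made of buckwheat flour without any herbal medicines; however is still mixed with honey". The procedure at the visit is summarised as "locate the acupoints, disinfect the skin, and attach the plaster on the skin over the acupoints".

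**The concern.** The protocol foresees a specific harm and plans how to respond to it, but its entry rule does not ask about the one thing that could identify some of the women at risk beforehand. A known allergy can be found with a question and damaged skin with a look, both before any plaster is applied.

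The exposure is not trivial. Five acupoints are treated, with nine sessions over three cycles, and each plaster stays on for hours. The Background section presents absorption through the skin as part of the rationale, and the Safety evaluation section allows for whole-body as well as local reactions. At stake is an avoidable reaction in a participant whose risk was already known to her.

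**Working it through.** No stated figure needs to be reproduced. The check is a reading of the relevant sections side by side.

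1. **Inclusion criteria.** 0 of 7 address allergy, hypersensitivity or skin condition.

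2. **Exclusion criteria.** 0 of 7 address them. Two items might seem to reach the point and do not. Item 2 speaks of contraindications but ties them to cardiovascular, liver and kidney disease. Item 5, on compliance, is defined by failure to understand the study or to complete the diary.

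3. **Is the list operative?** Yes. The criteria are printed as complete numbered lists with no pointer to further conditions, and the Randomization section allocates the subjects who qualify. Applied exactly, the lists admit a woman with a known allergy.

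4. **Safeguards before exposure.** The summarised steps are to find the points, disinfect and attach. The Interventions section repeats the same three steps when describing operator training. Neither place mentions an allergy question or a skin check.

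5. **Safeguards after exposure.** Removal on reaction, symptomatic treatment and follow-up are all stated, and all start after a reaction has begun.

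6. **Which arms are exposed to what.** Honey and the sticky plaster are in both AHP and APP, the ten herbal ingredients in AHP only, and buckwheat in APP only. With 60 women per arm and 180 in total, the chance of being assigned to a plaster containing the relevant material is:
   - honey or adhesive: (60 + 60)/180 = 2/3;
   - a herbal ingredient: 60/180 = 1/3;
   - buckwheat: 60/180 = 1/3.

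   These fractions restate the allocation ratio for a woman who already has the allergy. They are not rates of harm. They do show that screening for the herbs alone would be too narrow. Waiting-list women also meet the AHP materials if they accept the treatment offered at completion.

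7. **Could the practitioner resolve it at the visit?** Only in part. Practitioners are blinded to which paste is used, so for a herb or buckwheat allergy they cannot tell whether the plaster in hand contains the problem ingredient. A decision at the visit also comes after randomisation. The protocol has an earlier opportunity: "During a run-in period of three menstrual cycles prior to randomization", candidates are already under observation and keeping a diary.

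**The case against.** The strongest reply is that this is a journal article. The full protocol, the consent text, the training videos and the operating procedures are not shown, and any of them might contain an allergy question. Certified acupuncturists with at least five years' experience apply the plasters, written consent comes first, and the summary of steps does not claim to be the complete visit procedure. The article also reports that earlier clinical observations found the formula safe in plaster form, and its list of possible harms ends with other mild effects.

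Much of this stands as a limit on certainty. It does not remove the point, because eligibility is printed as a full list that decides who is randomised, and nothing in the article signals a further criterion. General reports of safety do not speak to women with a known allergy.

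A reader might infer more than the documents support, in three ways:

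- **That women with known allergies will in practice receive the plaster.** The text shows that they are eligible, not that no one would ask or that any have been treated.
- **That the protocol identifies honey, buckwheat or adhesive as allergens, or broken skin as a hazard.** It attributes allergic responses and local infections to the AHP and lists the other items only as materials. Including them, and skin condition, is a reasonable clinical extension and should be labelled as such.
- **That the gap biases or weakens the AHP versus APP comparison.** The documents give neither a prevalence nor a rule for withholding plasters, so any figure for an effect on the analysis would rest on an invented scenario.

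**Conclusion.** The gap is real and worth closing. None of the 14 printed eligibility criteria covers known hypersensitivity or damaged skin, although the protocol names allergic responses and local infections as possible harms of the AHP, and its stated protections follow exposure. The ground is participant safety alone. The primary outcome, the sample size of 180 and the planned analyses are untouched, and the number of women affected cannot be stated from the documents.

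The conclusion assumes that the printed lists are the lists in use. If the full protocol or the operating procedures already contain such a screen, the sponsor need only confirm it and print it. Confidence is therefore medium.

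**What to change.** Add an eighth exclusion criterion, applied to every candidate before randomisation whatever arm she might enter: known hypersensitivity to any ingredient of the herbal formula, to honey, to buckwheat or to the plaster adhesive, or broken or diseased skin at an application site.

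Because the Trial status section says recruitment is ongoing, put the same question to:

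- women now in the run-in, before they are randomised;
- women already randomised to a plaster arm, before their next session. If the answer is positive, withhold the plaster whichever arm it belongs to, so that the blind is kept. Continue their follow-up and keep them in the full analysis set, which the plan defines as all randomised participants;
- waiting-list women, before they take up the optional AHP.

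The cost is one screening question, a brief skin inspection and a short amendment. The downside is that a few women become ineligible. No sample-size or analysis figure needs to change.
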